### Post-enrolment data collection

The listed information is collected at baseline following witnessed, informed consent. Human ethics approval has been provided for witnessed oral consent to be obtained where impaired upper limb function limits the ability of potential participants to provide written consent.

1. Demographic information (age at injury, sex, date of injury).

2. Time and date of assessment.

3. Current lesion level and completeness (Abbreviated Injury Scale score).

4. Medical history.

5. Height and weight.

6. Current medications.

7. Whether the subject has any intercurrent illness.

8. Likelihood of undiagnosed, pre-existing OSA (Multivariate Apnoea Prediction Index
[20].

9. Abdominal girth at end-expiration and neck circumference.

10. Sleep studies.

The presence of OSA will be assessed using a portable sleep monitoring device, which comprehensively measures respiratory and sleep variables. (Compumedics™ Somté PSG, Abbottsford, Australia). All studies will be sleep-staged and respiration-scored by an independent trained sleep scientist. Sleep will be staged in 30-second epochs, arousals marked and respiratory events scored according to international standard criteria
[21]. Summary indices and statistics will be calculated. Heart rate variability will be calculated from the ECG trace taken during quiet resting (prior to sleep onset).

All participants with an apnoea hypopnoea index (AHI) ≥ 10 will be considered as positive OSA cases and will proceed to have baseline measures (below) taken.

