The specific aim of the COSAQ study is to determine the effect of nocturnal auto-titrating CPAP treatment on neuropsychological function, quality of life, autonomic dysfunction and breathing in people with acute quadriplegia and OSA. To address this aim, one primary and two secondary hypotheses were developed and will be tested. The primary hypothesis is that usual care and nocturnal CPAP treatment will improve neuropsychological functioning more than will usual care alone; specifically, working memory as tested on the Paced Auditory Serial Addition Test (PASAT). The first secondary hypothesis is that the magnitude of improvement in neuropsychological function will be predicted by the severity of baseline sleepiness (Karolinska Sleepiness Scale (KSS)), sleep fragmentation (Sleep Efficiency, Arousal Index) and sleep apnoea (apnoea hypopnoea index (AHI), percentage total sleep time with SpO_2_ < 90%). The second secondary hypothesis is that usual care and nocturnal CPAP will improve the following parameters more than usual care alone:

1. Sleepiness and symptoms: Karolinska Sleepiness Scale (KSS) and the Basic Nordic Sleep Questionnaire (BNSQ).

2. Lung Function: spirometry.

3. Quality of life: Assessment of Quality of Life (AQoL).

4. Autonomic dysfunction: event diary and heart rate variability.

5. Health utility: AQoL-derived change in utility and associated quality-adjusted life years (QALY).

6. Depression and anxiety: Hospital Anxiety and Depression Scale (HADS) and the Profile of Mood States (POMS).

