### Baseline measures

A number of tests are made prior to the trial of CPAP and randomization.

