### End study (three months or hospital discharge) data collection

The baseline testing battery will be repeated in the same manner with the exception of the Multivariate Apnoea Prediction Index. Following the completion of all testing procedures, a semistructured subject interview will be held with a subset of the trial participants to examine their experience of the trial and to explore themes related to adherence. The sleep study will be repeated, with the subjects using their CPAP (or not) as randomized. At this time, participants will be provided with full details of their physiological tests and referred for ongoing clinical management of any OSA if they wish.

An adverse event audit will be performed at the conclusion of the study. This process will be overseen by an independent outcomes committee comprising two sleep or spinal specialist clinicians. The patient medical record will be audited for all adverse events defined by the outcomes committee. The blinded assessor at each site will perform the audit. The outcomes committee will review the standardized audit report and will classify any defined event by severity and whether it was or was not likely to have been associated with study treatment or assessment procedures. These classified event reports will be passed to the independent data monitoring and review committee for review.

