#### Unable to continue with CPAP

Any participant who chooses to cease CPAP treatment will remain in the study for 3 months. The test collection battery will proceed as planned.

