### Estimated subject numbers

This is a three-month treatment trial at a time where there is profound disruption in the life of the study participants. Over this acute period, direct measurements of quality of life and performance in rehabilitation will not demonstrate the efficacy or otherwise of CPAP. The feasibility study clearly demonstrated that there was substantial variability in quality of life post injury, unrelated to OSA or CPAP, thus rendering these outcomes unsuitable for demonstrating short-term improvement in a study sample of constrained size. We are, therefore, basing our sample size calculations on neurocognitive performance, a number of measures of which form our test battery. The specific neurocognitive test in the test battery, which is best characterized in both the spinal population and OSA, is the PASAT. Lower (worse) PASAT scores correlate with sleep fragmentation severity in the able-bodied
[31] and OSA severity in quadriplegia
[15]. Lower PASAT scores are also associated with diminished frontal lobe function, as assessed by functional magnetic resonance imaging
[32] and a mean difference in PASAT scores of seven discriminates between those with and without cognitive impairment in multiple sclerosis
[33]. In the able-bodied with OSA, those adherent to CPAP over three months have a PASAT score 18 units higher than those who are not (standard deviation of 33)
[34].

Assuming a mean difference between the study arms of 18
[34], a standard deviation of 33, a power of 0.8, an *α* value of 0.05 and a nonadherence to CPAP rate of 15%, 150 subjects will be randomized. To ensure that 150 participants complete the study, we estimate that approximately 820 admissions with quadriplegia will be required across our collaborating centres (at least 8 of 44 admissions will meet the inclusion criteria, fail to meet the exclusion criteria, agree to participate, have OSA and tolerate CPAP). This sample is also adequate to detect any true difference between secondary outcomes, such as sleepiness (KSS number required = 44).

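### The protocol does not keep the end-study resting ECG for heart rate variability off CPAP, so the between-arm comparison can confound an acute device effect with a change in autonomic function

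*Protocol article*

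**What the plan says.** The article lists HRV with the symptom diary as an outcome (Background, hypotheses): "Autonomic dysfunction: event diary and heart rate variability". It falls under a between-arm hypothesis: "The second secondary hypothesis is that usual care and nocturnal CPAP will improve the following parameters more than usual care alone".

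The source of the measure is given under Post-enrolment data collection, in the description of the sleep study: "Heart rate variability will be calculated from the ECG trace taken during quiet resting (prior to sleep onset"). Baseline is off the device, because under Baseline measures "A number of tests are made prior to the trial of CPAP and randomization", and the sleep study that establishes OSA comes before the CPAP run-in.

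Two sentences under End study data collection bear on the follow-up recording. The general one is "The baseline testing battery will be repeated in the same manner with the exception of the Multivariate Apnoea Prediction Index". The one specific to the sleep study is "The sleep study will be repeated, with the subjects using their CPAP (or not) as randomized".

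No section says whether the mask is on and delivering pressure during the resting segment, and none provides a separate off-device ECG for the CPAP arm.

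**The concern.** The HRV measurement is tied to a session whose conditions differ by arm at end study but not at baseline. The segment lies before sleep onset. A participant who is to sleep on CPAP may well be wearing the mask by then. In that case one arm is recorded under positive pressure and the other while breathing freely.

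Positive pressure alters breathing pattern and intrathoracic pressure, and it is reasonable to expect both to affect beat-to-beat variability. An arm difference in HRV could then arise with no change in underlying autonomic function, or a real change could be masked. Such an error would follow allocation, so randomisation, blinded scoring and a larger sample would not remove it. It could be separated at analysis only if device status during the segment were known.

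**Working it through.** The plan states no effect size, SD, power or sample size for HRV, so there is no figure of its own to reproduce. The check is a reading of the sections together, followed by an illustration on assumed values.

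**Recording condition by arm and visit**

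| Visit | CPAP arm | Usual care | Basis |
|---|---|---|---|
| Baseline | off device | off device | Baseline measures; Pre-randomization procedure |
| End study, sleep study as a whole | on CPAP | off CPAP | End study data collection |
| End study, resting segment before sleep | not stated | off CPAP | no section fixes it |

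The last row is the gap. Two stated rules, HRV from the sleep-study ECG and the sleep study run as randomized, together allow the resting segment to differ by arm. They probably lead to it, but they do not require it.

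The CPAP arm need not be uniform either. Under Unable to continue with CPAP, "Any participant who chooses to cease CPAP treatment will remain in the study for 3 months", with testing as planned, so some of that arm may be off the device at end study. Under Randomized group cross-over, usual-care participants who go on to CPAP or noninvasive ventilation stay in their allocated group.

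**Illustration of size**

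From the document: N = 150. Assumed: equal arms of 75, no change in underlying autonomic function, and an acute shift of d SD in every CPAP-arm participant and in no usual-care participant. The values of d are chosen for illustration.

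For a two-sided 5% two-sample t-test with 148 degrees of freedom (critical value 1.976), the noncentrality is d × √(75/2) = d × 6.124. The rejection rate is the probability that a noncentral t with that parameter falls outside ±1.976.

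| Assumed shift d | Noncentrality | Rejection rate (5% if no shift) |
|---|---|---|
| 0.1 SD | 0.612 | 9% |
| 0.2 SD | 1.225 | 23% |
| 0.3 SD | 1.837 | 45% |
| 0.5 SD | 3.062 | 86% |

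A normal approximation gives 9%, 23%, 45% and 86% (0.094, 0.232, 0.451, 0.865).

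**Dilution**

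The sample-size section plans for 15% nonadherence to CPAP. If only 85% of the CPAP arm were on the device during the segment, the mean shift would be 0.85 × d, that is 0.085, 0.17, 0.255 and 0.425 SD. Treating the SD as unchanged, the rejection rates fall to 8%, 18%, 34% and 73%. Controls using CPAP, or sites that record before fitting the mask, would lower them further. The first table is therefore an upper bound for each assumed shift.

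**The case against.** The strongest reply is that the article never says the mask is on during the rest. HRV comes from a distinct awake segment, and the general end-study sentence says testing is repeated as at baseline, when the rest was off the device. A reader might infer from the sleep-study sentence that the arms are certainly measured under different conditions. The document does not support that. The sleep-study sentence is the more specific of the two and makes on-device recording likely, but mask timing is simply not fixed.

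Second, a reader might take the comparison to be biased against the trial's own question. That also goes too far. The hypothesis concerns CPAP plus usual care against usual care and does not say that the benefit must persist with the device off. Against an on-treatment question, an on-device value is a legitimate measure. Listing HRV beside a symptom diary as a marker of autonomic dysfunction suggests the participant's own state, but does not settle the matter.

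Third, neither the existence nor the size and direction of an acute effect is in the document. This stands: the rejection rates are ordinary t-test power at chosen shifts, not estimates for this trial.

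Fourth, mask timing could be called operational detail that an article leaves to the full protocol or a site manual. This stands only in part. The article itself states both the source of HRV and the arm-specific condition of that source, and it is the combination that leaves the comparison exposed.

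**Conclusion.** The concern holds in conditional form. As written, the protocol does not keep the end-study resting segment off CPAP, although the sleep study it comes from is on CPAP in one arm only and baseline was off CPAP in both. If the mask is on, the HRV comparison can confound an acute pressure effect with a change in underlying autonomic function.

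The possible size is unknown. The range of 9% to 86% false-positive results for shifts of 0.1 to 0.5 SD rests on assumed shifts, equal arms of 75, no underlying change, all CPAP-arm participants on the device and no usual-care participant on it. It shows only that even a modest acute shift would matter.

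The reach is narrow: one of the two measures under one of six items in the second secondary hypothesis. The primary PASAT comparison and N = 150 do not depend on it. A change is worth making because the remedy is nearly free and removes a possible arm-dependent bias that analysis alone may not be able to undo.

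**What to change.** State that HRV is calculated, at baseline and end study and in both arms, from a resting ECG of fixed length recorded before the CPAP mask is fitted, and that this segment is used for the between-arm comparison. If an on-device value is also wanted, report it separately and label it as such.

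For participants already tested, use the device log to flag whether CPAP was on during the segment. Report HRV by that flag, labelling on-CPAP values as on-device measures. Do not exclude them: exclusion would fall almost only on the CPAP arm, and on its device users, and would conflict with the intention-to-treat statement under Data analysis.

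The cost is a few minutes of extra recording on the same equipment, a line in the site instructions, and a flag on existing records. Only the measurement changes; treatment does not.

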### Baseline measures

A number of tests are made prior to the trial of CPAP and randomization.

#### Cognitive test battery

•Rey Auditory Verbal Learning Test.

•Digit Span sub-test of the Wechsler Adult Intelligence Scale Revised.

•Paced Auditory Serial Addition Test (PASAT).

•Symbol Digit Modalities Test.

•National Adult Reading Test.

All these tests have been previously employed to show neurocognitive limitation in those with quadriplegia and OSA
[15]. They are all administered orally, so that written replies or motor responses are not required. This battery of tests takes approximately 40 minutes to complete and measures function in the following areas: short-term memory, attention and concentration, immediate memory span, cognitive flexibility, internal scanning, working memory, visual perception, visual attention and concentration. Previous authors have found that patients with quadriplegia and OSA had deficits in attention, concentration, memory and learning skills
[15]. The significance of poor function in these areas is greater in the quadriplegic population, owing to their limited physical functioning. As a result, cognition becomes even more important for optimal participation in rehabilitation and society. Moreover, it is to be expected that performance on these tests will be improved by CPAP treatment.

#### Sleep symptoms and functional consequences of sleepiness

The Basic Nordic Sleep Questionnaire (BNSQ)
[22] has been validated in a spinal cord injured population and will provide additional information about sleep quality.

#### Quality of life and health utility values

The Assessment of Quality of Life (AQoL)
[23] is a generic quality of life instrument and has been found to be as good as or better than instruments commonly used in measuring outcomes in stroke, co-ordinated care, influenza, cochlear implants, population monitoring and elderly groups. The AQoL provides both health-related quality of life information in the domains of ‘illness’, ‘independent living’, ‘social relationships’, physical senses’, ‘psychological wellbeing’ and a total AQoL value. In addition to these outcomes, the AQoL may be summarized to generate utility values, thereby enabling the generation of quality-adjusted life years (QALY) and facilitating economic analyses.

#### Other tests

In addition, the Hospital Anxiety and Depression Scale (HADS) and the Profile of Mood States (POMS) tests will be used.

### Pre-randomization procedure

All subjects who fulfil the inclusion criteria, are not excluded by the exclusion criteria, consent to participate and are classified with positive OSA will be trialled on auto-titrating CPAP (Resmed AutoSet, San Diego, USA) for up to three nights.

Subjects who are able to use the CPAP for at least four hours on any night will then be randomized as soon as they have succeeded in doing so, into either the treatment or usual care group. If four hours’ use are tolerated on the first night, subjects will be randomized at this time. Those who do not use the CPAP for four hours on any of the three nights will cease participation in the trial. The four-hour cut off was derived from the feasibility trial, where those who were unable to achieve this time were not likely to be compliant over the length of the trial.

The decision to randomize only those who are likely to be adherent with CPAP was the most significant study design modification to arise from the feasibility study. A rate of nonadherence of 50%, as was observed in the feasibility study, would render this study unfeasible. Pre-randomization selection potentially limits the study generalizability to those who are tolerant of CPAP, although it accurately reflects clinical practice (you would never ‘force’ patients to use a therapy they did not accept), was strongly supported by the Australasian Sleep Trials Network, is a similar protocol to that employed in the multinational Sleep Apnoea Cardiovascular Endpoints study
[24] and significantly increases the project feasibility by reducing the numbers of subjects, the timeframe and the associated staff cost.

### Randomization

Randomization will be performed centrally using the research study database
[25]. A blocked, randomization sequence was generated
[26] and loaded into the online database by an independent member of the research unit prior to trial commencement. Allocation concealment is assured through the site design, which requires subject enrolment be completed before randomization can become possible. Additionally, the randomized group is only revealed after a commitment to randomization is both made and confirmed.

### Weekly measures

The following measures will be made at baseline and then weekly upon review:

1. Time and date of assessment.

2. Current medications.

3. Any intercurrent illness.

4. Sleepiness, using the Karolinska Sleepiness Scale (KSS)
[27], a ten-item scale, which describes current sleepiness (state).

5. Machine usage data in the CPAP treatment group will be downloaded weekly, and those subjects in the CPAP treatment group will be reviewed with respect to any machine usage or masking issues.

6. Clinical review, autonomic dysfunction assessment and troubleshooting.

All participants will be provided with an autonomic dysfunction symptom diary (Table 
1). The diary will record the number, nature and treatment of symptoms typically related to autonomic dysreflexia.

**Table 1 T1:** Autonomic dysreflexia diary

	**Number of events**	**Treated****(yes/****no)**
Pounding headache, which gets worse		
Flushing and blotching of the skin above the level of the spinal cord injury		
Profuse sweating		
Chills without fever		
Hypertension (high blood pressure)		

In the last week, have you experienced any of the following symptoms, and if so, were they treated?

### Monthly measures

Respiratory function will be measured at baseline and then monthly upon review. All testing will be performed in the supine position. Simple spirometry will be used to obtain vital capacity and forced expiratory volume in 1 second. All tests of respiratory function will be performed without an abdominal binder and in accordance with the performance limitations imposed by quadriplegia
[28].

### End study (three months or hospital discharge) data collection

The baseline testing battery will be repeated in the same manner with the exception of the Multivariate Apnoea Prediction Index. Following the completion of all testing procedures, a semistructured subject interview will be held with a subset of the trial participants to examine their experience of the trial and to explore themes related to adherence. The sleep study will be repeated, with the subjects using their CPAP (or not) as randomized. At this time, participants will be provided with full details of their physiological tests and referred for ongoing clinical management of any OSA if they wish.

An adverse event audit will be performed at the conclusion of the study. This process will be overseen by an independent outcomes committee comprising two sleep or spinal specialist clinicians. The patient medical record will be audited for all adverse events defined by the outcomes committee. The blinded assessor at each site will perform the audit. The outcomes committee will review the standardized audit report and will classify any defined event by severity and whether it was or was not likely to have been associated with study treatment or assessment procedures. These classified event reports will be passed to the independent data monitoring and review committee for review.

### Treatment device

Participants in the treatment group will be fitted with a nasal or face mask and head gear. The choice of patient interface will be made locally by the treating teams. The CPAP will be delivered by an auto-titrating device (Resmed AutoSet, San Diego USA). These devices automatically set the level of delivered pressure to ensure upper airway patency, thereby eliminating the need for a pressure titration sleep study to be performed in the sleep laboratory. In addition, if, as was observed in the pilot study, effective CPAP alters over the trial period
[19], the device will alter the delivered pressure accordingly to maintain airway patency.

The AutoSet devices record the number and type of respiratory events detected, the pressure delivered in response to these events and the amount of time that the machine was on and delivering pressure to a patient. If the machine is running, but the mask has been removed from the face, this time does not contribute to the measure of CPAP compliance.

### Feasibility, safety and efficacy

The research team have completed a one-year study examining the feasibility and safety of the planned protocol. No major adverse events were observed; in particular, no episodes of excess uncontrolled flow, such that exhalation was impeded by the auto-titrating CPAP were observed
[19]. One device was found to be faulty and exchanged. This fault did not affect any participant. All minor adverse events (mask irritation, nasal stuffiness) related to acclimatization to CPAP and are common to all new CPAP users.

